### Ethics, study registration and consent

The final protocol was approved by the Ethics Committee of the First Affiliated Hospital of Anhui Medical University (PJ2019-17-12). The trial protocol was registered at the ClinicalTrials.gov protocol registration system (NCT04218669). Patients with HL who are scheduled for common bile duct exploration at the Department of General Surgery, Anhui Medical University, will be screened for eligibility and informed about the trial. The study procedure, benefits, risks and data management will be clarified in detail during the conversation.

### Trial interventions

All patients with SOL underwent common bile duct exploration and complete stone extraction. The surgical procedures of the T-tube drainage arm and Roux-en-Y HJ arm are as follows.

#### Group A: T-tube drainage

A T-tube was placed for biliary drainage, and the common bile duct was intermittently sutured with 4-0 Vicryl sutures.

#### Group B: Roux-en-Y HJ

The common hepatic duct was cut, and the duodenal side was closed with sutures. The small intestine was cut off 15 cm below the ligament of Treitz. The distal end was lifted, and a 1–2-cm incision was made at the jejunal wall 4–5 cm from the jejunal stump. The anastomosis used 5-0 PDS II with double-armed inside-out sutures in the jejunum and outside-in sutures in the hepatic duct. One side of the needle was used to continuously penetrate and suture the whole layer of the posterior lateral wall of the jejunum and the posterior lateral wall of the biliary duct, and the other side of the needle was used to continuously suture the anterior part of the anastomosis. Mucosa-to-mucosa contact should be ensured with every stitch. The anastomotic stomas were then checked for leakage. The enteric-enteric anastomosis was performed 60 cm below the site of the hepaticojejunal anastomosis.

### Primary and secondary endpoints

All participants will be followed up regularly according to the schedule shown in Fig. 2 at the stated intervals after surgery for at least 3 years. At the follow-up visits, patients will undergo laboratory tests and abdominal ultrasonography as described in Fig. 2. CT or MRI will be performed in cases of suspected stone recurrence or cholangitis. Laboratory tests mainly include routine blood, liver and kidney function, electrolytes, procalcitonin, C-reaction protein, carcinoembryonic antigen, carbohydrate antigen 199 (CA199) and alpha-fetoprotein (AFP).

The primary efficacy endpoint of the trial will be the incidence of biliary complications (stone recurrence, biliary stricture, cholangitis). Stone recurrence will include any bile duct stones detected with any imaging modality during follow-up. Biliary stricture will be defined as clinically evident stenosis and subclinical stenosis proven by endoscopic examination or reoperation. The diagnosis of cholangitis will be based on clinical evidence (abdominal discomfort/pain, jaundice or fever associated with hepatolithiasis).

The secondary outcomes will be the surgical, perioperative and long-term follow-up outcomes. The surgical outcomes will include operative duration, intraoperative blood loss, intraoperative blood transfusions, stone distribution and SO function. The perioperative events occurring within 90 days after surgery will be recorded, including biliary leakage, wound infection, pulmonary infection, reoperation, hepatic injury, haemorrhage, bowel function recovery, intra-abdominal fluid collection or abscess, mortality, duration of postoperative hospital stay and total hospitalization expenditure. The indices of long-term follow-up outcomes will be hepatic injury, stone recurrence, biliary stricture, rate of unplanned readmission for HL, incidence of cholangitis and quality of life. Postoperative complications will be graded based on severity according to the Clavien-Dindo definition (shown in Additional file 2: Table S1) [8]. Long-term quality of life will be assessed by clinical grading according to Terblanche et al. [9]. Grades I and II constituted excellent or good results, grade III fair and grade IV poor (shown in Additional file 2: Table S2).

Laboratory examination routinely collects patient blood samples in the ward or clinic. The blood samples store at room temperature and test in the laboratory of our hospital that day. The specific time laboratory examination and abdominal ultrasonography are shown in Fig. 2, and the perioperative laboratory examination time is the first day, the third day, and the seventh day after the operation.

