**Methods/design:**

In total, 210 patients who met the following eligibility criteria were included and were randomized to the choledochojejunostomy arm or T-tube drainage arm in a 1:1 ratio: (1) diagnosed with hepatolithiasis with SOL during surgery; (2) underwent foci removal, stone extraction and stricture correction during the operation; (3) provided written informed consent; (4) was willing to complete a 3-year follow-up; and (5) aged between 18 and 70 years. The primary efficacy endpoint of the trial will be the incidence of biliary complications (stone recurrence, biliary stricture, cholangitis) during the 3 years after surgery. The secondary outcomes will be the surgical, perioperative and long-term follow-up outcomes.

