### Standardization of perioperative care

The operations will be performed by two senior surgeons ([name] and [name]) who are equally skilled in T-tube drainage and Roux-en-Y HJ. Intraoperative flexible choledochoscopy (CHF-P20, external diameter, 4.9 mm; Olympus, Tokyo, Japan) will be routinely performed to explore the biliary ducts, identify the function of the SO and remove residual stones. All patients included in the study should successfully undergo cleaning of all ductal stones, removal of all strictures and elimination of the non-functioning liver segments that harbour bacteria and serve as foci of infection. For the patients with T-tubes, cholangiography will be performed to ensure that all the stones are clean before the T-tubes are removed. If there are residual stones, they could be cleaned through postoperative choledochoscopy. Indications for liver lobe resection will include a liver segment or lobe filled with stones that were inaccessible by other approaches for treatment, strictures associated with stones, atrophy of the affected liver segments or lobe, presence of liver abscess, or suspected cholangiocarcinoma. The selection criteria for hepatectomy will require patients to have Child’s A grade liver function and no evidence of portal hypertension. The grading criteria for SO function are as follows: normal—the shape of the SO is circular (Fig. 3a) or comma-like (Fig. 3b) with normal rhythmic contractions, a flexible choledochoscope cannot enter the duodenum and the SO can completely close without gaps during closure; SOL (shown in Additional file 3: Video S1-Grading criteria for the SO function laxity)—the shape of the SO is oval (Fig. 3c) or irregular (Fig. 3d), a flexible choledochoscope can enter the duodenum with some resistance, the SO cannot completely close during closure or reflux of food or methylene blue can be seen in the common bile duct during flexible choledochoscopy; and loss of function—the flexible choledochoscope can directly enter the duodenum, and no contractions are observed after the morphine-neostigmine test.

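### The recurrence definition does not separate residual from recurrent stones, while a pre-removal cholangiogram is scheduled in the T-tube arm only, so counting of primary events depends on the arm

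*Protocol article*

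**What the plan says.** Under Primary and secondary endpoints, the article defines the stone component of the composite: "Stone recurrence will include any bile duct stones detected with any imaging modality during follow-up". It sets no stone-free baseline, no minimum interval and no exclusion of residual stones. The Methods/design part of the abstract gives the window: "incidence of biliary complications (stone recurrence, biliary stricture, cholangitis) during the 3 years after surgery". No later starting point is stated.

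The imaging common to both arms is also under Primary and secondary endpoints: "At the follow-up visits, patients will undergo laboratory tests and abdominal ultrasonography as described in Fig. 2", and "CT or MRI will be performed in cases of suspected stone recurrence or cholangitis". The legend of Fig. 2 puts the first of the listed visits at 3 months.

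Standardization of perioperative care adds an examination for one arm: "For the patients with T-tubes, cholangiography will be performed to ensure that all the stones are clean before the T-tubes are removed". It then says: "If there are residual stones, they could be cleaned through postoperative choledochoscopy". No counterpart is described for HJ patients.

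Under Exclusion criteria, patients with stones left at surgery are kept out. Under Randomization and blinding, the envelope is opened after duct exploration, and surgeons and patients are not blinded.

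**The concern.** The same stone gets two labels. A stone on the pre-removal cholangiogram meets the endpoint definition, because it is a bile duct stone seen on imaging within 3 years of surgery. The perioperative section calls it residual. Eligibility cannot remove it, because the exclusion covers only stones seen at operation and the cholangiogram comes after randomisation.

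The chance that a residual stone is found, and when, therefore depends on the arm. In the T-tube arm a cholangiogram in every patient looks for it. In the HJ arm it must show on visit ultrasonography, or raise enough suspicion to prompt CT or MRI. The trial is open-label and the article describes no blinded outcome assessor, so the labelling would fall to staff who may know the arm. What is at stake is whether a difference in the primary composite reflects the drainage method or the way stones were looked for and labelled.

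**Working it through.** The plan gives no figure on this point to reproduce. The text comes first, then the size.

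**1. The two possible rules**

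- *Cholangiogram stones count.* The T-tube arm gains events from an examination that the HJ arm does not have. HJ residual stones count only if ultrasonography, CT or MRI finds them. The bias is against T-tube drainage, in the direction of the planning assumption (30% T-tube, 15% HJ).
- *Cholangiogram stones are cleared and not counted.* T-tube patients go on with those stones removed and no event recorded. An equivalent stone in an HJ patient stays in place and, if seen later, counts as recurrence. The bias is against HJ.

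**2. Inputs for the size**

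- From the article: 105 per arm, 1:1 allocation, two-sided test, P < 0.05, Fisher's exact test for categorical data.
- Assumed: true 3-year risk of 20% in both arms (no treatment effect), between the planning rates of 15% and 30%.
- Assumed: r, the share of T-tube patients with a residual stone on the cholangiogram, independent of other events. The article gives no rate, so r is varied.
- Assumed: HJ imaging finds either none or half of such stones.

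**3. Formulas**

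- Observed T-tube rate = 0.20 + 0.80 × r
- Observed HJ rate = 0.20 if none are found, or 0.20 + 0.80 × r/2 if half are found
- False-positive rate = sum of the binomial probabilities of all tables with 105 per arm for which two-sided Fisher P < 0.05

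Example at r = 10%: T-tube 0.20 + 0.80 × 0.10 = 0.28; HJ 0.20, or 0.20 + 0.80 × 0.05 = 0.24.

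**4. Results**

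| r | T-tube rate | HJ rate, none found | Fisher false-positive rate | HJ rate, half found | Fisher false-positive rate |
|---|---|---|---|---|---|
| 0% | 20.0% | 20.0% | 3% | 20.0% | 3% |
| 2% | 21.6% | 20.0% | 4% | 20.8% | 4% |
| 5% | 24.0% | 20.0% | 8% | 22.0% | 5% |
| 10% | 28.0% | 20.0% | 23% | 24.0% | 8% |
| 15% | 32.0% | 20.0% | 45% | 26.0% | 13% |

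Fisher's test is conservative here, with about 3% at r = 0. A pooled z-test with no HJ detection gives about 6%, 11%, 27% and 51% for r = 2%, 5%, 10% and 15%, against 5% at r = 0.

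**5. The opposite direction**

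Under the second rule, let s be the share of HJ patients whose missed stone surfaces later and is counted. The HJ rate is 0.20 + 0.80 × s against 0.20. With equal arms and a two-sided test, the columns for no HJ detection apply with the arms exchanged: s = 5% gives about 8%, now in favour of T-tube drainage.

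**The case against.** The best answer is that the cholangiogram was never meant as a recurrence assessment. It stands under perioperative care, it checks clearance before tube removal, and the article itself calls the stones residual. The definition counts stones found during follow-up, which can be read as the scheduled visits from 3 months on. Stone recurrence is also listed among the long-term outcomes and not among the 90-day perioperative events. This reading is reasonable, but it does not settle the matter. The stated window is the 3 years after surgery, the timing of the cholangiogram is not given, and the reading leads to the second rule above, which is also unequal between the arms.

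It is also fair to say that r may be small. Residual stones at surgery are excluded, and intraoperative choledochoscopy is routine. At r = 2% the effect is negligible. Severe inflation needs both a high r and little or no HJ detection.

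Some stronger readings are tempting, and the article does not support them:

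- *Residual stones become events in the T-tube arm only.* An HJ stone found on ultrasonography, CT or MRI counts under the same definition. The difference is in intensity and timing of detection.
- *T-tube patients have routine postoperative choledochoscopy.* It is conditional on residual stones; only the cholangiogram is planned for all T-tube patients.
- *The bias must favour HJ.* It depends on which rule is applied.
- *Strictures are affected in the same way.* The definition includes "subclinical stenosis proven by endoscopic examination or reoperation", and one might infer easier access through the T-tube tract. The article describes no routine postoperative endoscopy in either arm and does not state unequal access.

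**Conclusion.** The point holds as a defect in the endpoint rule. The article states a recurrence definition that takes in residual stones, and it schedules a sensitive examination for such stones in one arm after randomisation. Ascertainment of the primary endpoint therefore depends on the arm, whether the cholangiogram stones are counted or not. This is not detail left to a fuller document, because the definition is given and its wording conflicts with the perioperative section.

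The direction is not fixed. The size is unknown and spans the table above, from no material effect at r = 2% to a false-positive rate of about 45% at r = 15% with no HJ detection. All of it rests on the assumed r, the 20% base risk, independence from other events and the assumed HJ detection.

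**What to change.** Reconcile Primary and secondary endpoints with Standardization of perioperative care:

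- State that a stone seen on the pre-removal cholangiogram is residual and is not a recurrence.
- Base the stone component of the primary endpoint on examinations scheduled alike in both arms: visit ultrasonography, with CT or MRI on suspicion.
- Count it from one fixed landmark after surgery, the same in both arms. Class stones found before the landmark as residual in either arm.
- Record the method and date of detection on the case report form.
- Report residual stones by arm as a secondary outcome.
- Run a sensitivity analysis that counts all residual stones as events from surgery.

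Reclassifying the cholangiogram stones alone would not be enough: it would leave residual HJ stones counted while T-tube ones were not. Even with a landmark, an HJ stone that stays silent until after it can still count. The sensitivity analysis and the residual-stone report by arm show how much this matters.

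The cost is a change of endpoint wording and a short case report form entry, with no added examinations. The downside is somewhat fewer primary events, and so slightly less power. The change should be made before events are classified by staff who know the arm.

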### Randomization and blinding

To achieve comparable groups of known and unknown risk factors, randomization will be performed. Patients meeting the eligibility criteria will be randomly assigned (1:1) to the T-tube drainage arm or Roux-en-Y HJ arm by computer-generated allocation based on the envelope method and the hierarchical block randomization method. The envelopes will be opened after common bile duct exploration.

Blinding of the surgeons and patients is not feasible due to the obviously different characteristics of the two types of biliary drainage. However, the statisticians will be blinded to the treatment allocation during data collection and analysis.

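### Silent biliary strictures, part of the primary endpoint, count only on endoscopy or reoperation, which is neither planned nor equally accessible in the two arms

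*Protocol article*

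**What the plan says.** Under Primary and secondary endpoints, the protocol article makes the incidence of biliary complications (stone recurrence, stricture, cholangitis) the primary endpoint.

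- **Definition of stricture:** "Biliary stricture will be defined as clinically evident stenosis and subclinical stenosis proven by endoscopic examination or reoperation". It has two parts, a clinically evident form and a subclinical form with a proof requirement.
- **Scheduled tests:** "At the follow-up visits, patients will undergo laboratory tests and abdominal ultrasonography as described in Fig. 2".
- **Triggered tests:** "CT or MRI will be performed in cases of suspected stone recurrence or cholangitis". Suspected stricture is not named.
- **Stones:** the same section counts a bile duct stone seen on any type of imaging.

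The two operations leave the duct in different states.

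- **Hepaticojejunostomy (HJ) arm**, under Group B: "The common hepatic duct was cut, and the duodenal side was closed with sutures", and "The enteric-enteric anastomosis was performed 60 cm below the site of the hepaticojejunal anastomosis".
- **T-tube arm**, under Group A: the common bile duct is sutured around a T-tube. Under Standardization of perioperative care: "For the patients with T-tubes, cholangiography will be performed to ensure that all the stones are clean before the T-tubes are removed". It continues: "If there are residual stones, they could be cleaned through postoperative choledochoscopy". No postoperative duct examination is described for the HJ arm.

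On masking, under Randomization and blinding: "Blinding of the surgeons and patients is not feasible due to the obviously different characteristics of the two types of biliary drainage". Only the statisticians are described as blinded.

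**The concern.** The rule for proving a subclinical stenosis does not fit the tests that the plan provides. A silent narrowing seen on CT or MRI does not count by itself, and nothing in the plan leads to the endoscopy or reoperation that would make it count. Whether proof is sought is then decided case by case by people who know the allocation.

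This would matter less if the chance of obtaining proof were the same in both arms. The described anatomy suggests that it may not be. The HJ arm loses the route through the papilla, and its bile duct anastomosis lies beyond a 60 cm jejunal limb. The T-tube arm keeps the duct in continuity and has a tube tract for a time. The HJ arm also has a new anastomosis that could narrow.

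If silent strictures are found less often after HJ, the recorded composite rate in that arm is too low. That error runs in the direction of the planning assumption (30% with T-tube, 15% with HJ). A true excess of strictures after HJ could also be hidden. Neither blinded statisticians nor an intention-to-treat analysis can recover events that nobody looked for.

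**Working it through.** **1. Tests against the definition.** The article gives no stricture rate and no detection rate by arm, so there is no figure of its own to reproduce on this point.

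| Element | Scheduled | Triggered by suspected stricture | Proof of subclinical stenosis |
|---|---|---|---|
| Laboratory tests, ultrasonography | yes | – | no |
| CT or MRI | no | no (stones or cholangitis only) | no |
| Cholangiography | T-tube arm only, before tube removal | no | no |
| Choledochoscopy | no; T-tube arm, if residual stones | no | yes, as an endoscopic examination |
| Reoperation | no | no | yes |

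The only tests scheduled in both arms, and the only imaging that can be triggered in both, are not accepted as proof.

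**2. Which events are at stake.** A patient whose stricture comes with stones or cholangitis is already a primary event. A clinically evident stenosis counts without endoscopy. Only isolated, subclinical strictures remain. Let q be the shortfall in the recorded HJ rate from such missed events, relative to the T-tube arm.

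**3. From detection to q.** If s is the true rate of isolated silent stricture, equal in both arms, then q = s × (detection in T-tube arm − detection in HJ arm). All detection rates here are assumptions.
- With 70% against 20%: q = 0.5 × s, which is 1.5 points at s = 3%, 2.5 at 5% and 4 at 8%.
- With low detection in both arms, say 10% against 5%: q = 0.05 × s, which is 0.4 points even at s = 8%.

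**4. From q to a false result.** Assume equal true composite rates p, a T-tube arm recorded at a = p and an HJ arm recorded at b = p − q, with n per arm and a two-sided test at 0.05. The probability of a significant result favouring HJ is approximately

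Φ[(q − 1.96 × SE0) / SE1],

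where SE0 = √(2m(1 − m)/n), m = (a + b)/2, and SE1 = √(a(1 − a)/n + b(1 − b)/n).

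Example with n = 105, a = 0.25, b = 0.21: m = 0.23, SE0 = 0.0581 and SE1 = 0.0580. The argument is (0.04 − 1.96 × 0.0581)/0.0580 = −1.27, so the probability is 10.2%.

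With 105 per arm (the planned enrolment) and p = 25%:

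| q (points) | Normal approximation | Fisher's exact test |
|---|---|---|
| 0 | 2.5% | 1.8% |
| 1 | 3.7% | 2.6% |
| 1.5 | 4.4% | 3.2% |
| 2.5 | 6.2% | 4.6% |
| 4 | 10.2% | 7.7% |

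With 93 per arm (the number before allowance for withdrawal) and p = 30%, the normal approximation gives 3.5% at q = 1 point, 4.8% at 2, 11.5% at 5 and 34.9% at 10.

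Fisher's exact test is shown because Statistical analysis names it for categorical data. It is conservative and starts below 2.5%.

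**The case against.** The strongest reply is that little is at stake and that the imbalance is inferred.

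- **Clinically evident stenosis counts in either arm.** A reader might infer that the whole stricture component lacks any qualifying test. The definition does not support that: on its natural reading, the proof requirement attaches to the subclinical form. What remains is that the evident form has no stated criterion.
- **The composite absorbs most symptomatic strictures.** This stands, and it limits the point to isolated silent ones.
- **Easier proof in the T-tube arm is not stated.** A reader might infer that proof is far easier there. The article ties choledochoscopy to residual stones, and stones left at operation are an exclusion criterion. Access through the tube ends when it is removed, cholangiography is not an accepted proof, and reoperation is possible in both arms. Different access follows from the described anatomy, but its degree is not documented.
- **A 70% detection rate fits poorly with a plan that schedules no endoscopy.** This also stands. If symptom-free patients are rarely examined endoscopically, detection is low in both arms and the difference small.
- **The article condenses a fuller protocol.** Detailed work-up rules may be there, and Fig. 2 is not shown. But the article itself states the proof rule, the visit tests and the imaging trigger, and these do not fit together.

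The reply reduces the size and certainty of the problem. It does not supply a way of confirming silent stricture that works alike in both arms.

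**Conclusion.** The concern holds for the subclinical part of the stricture definition. As written, the plan has no arm-neutral way to ascertain it: the accepted proofs are neither scheduled nor triggered for stricture, the treating side is unblinded, and access to the duct differs by arm. Unequal detection is a real risk, and its plausible direction favours hepaticojejunostomy.

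A reader might go further and conclude that strictures are under-counted in that arm. The documents do not show this. They give neither stricture incidence nor detection rates, so the size of any bias cannot be derived from them. Under the stated assumptions (equal true rates of 25% or 30%, 93 or 105 per arm), the effect is small at 1 to 2 points of missed stricture-only events. It is material at about 4 to 5 points, and 4 points already needs a silent-stricture rate of 8% with a 50-point gap in detection.

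This is a should-consider point. What recommends action is that the remedy is cheap and must be in place before outcomes are collected.

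**What to change.** Make two changes to the wording under Primary and secondary endpoints, applied identically in both arms.

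1. Accept stenosis documented on CT or MRI as proof of subclinical stricture, alongside endoscopy and reoperation, by criteria that the investigators specify in advance. The section already accepts imaging for stones.
2. Add suspected stricture to the existing CT/MRI trigger, keyed to tests already scheduled, for example new duct dilatation on the visit ultrasound or a cholestatic pattern in the liver tests.

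The cost is a few additional triggered scans of a type already in use, plus the amendment. The allocated operations do not change.

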### Eligibility criteria

#### Inclusion criteria

The following are the inclusion criteria:
Aged between 18 and 70 yearsDiagnosed with HL with SOL during the operationUnderwent foci removal, stone extraction without residue and stricture correction during the operationProvided written informed consentWas willing to complete a 3-year follow-up.

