### Statistical analysis

The two-sided null hypothesis for the primary outcome measure states that both study interventions lead to a similar rate of stone recurrence; the alternative hypothesis is that one intervention will perform better than the other. The continuous variables will be recorded as the mean ± SD (for normally distributed variables) or medians and interquartile ranges (for skewed parameters) and will be statistically analysed with Student’s *t* test and the non-parametric Mann-Whitney *U* test, respectively.

Categorical data will be presented as frequencies and group percentages and compared with Fisher’s exact test. Graded data, including age, quality of life and Clavien-Dindo classification, will be compared with the Wilcoxon signed-rank test.

The odds ratio for having biliary complications will be determined with a logistic regression model. The homogeneity of the two groups will be described by comparing the demographic data and the baseline values.

All analyses will be performed on an intention-to-treat (ITT) basis. Statistical Package for the Social Sciences (SPSS) 10.0 (SPSS Inc., Chicago, IL, USA) will be used for statistical analysis. Statistical significance will be defined as *P* < 0.05.

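### Operative time, blood loss and transfusion carry variation from surgery done before allocation; the comparison of means is unbiased but can lose precision unless values at envelope opening are recorded and adjusted for

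*Protocol article*

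**What the plan says.** All of the following is in the Protocol article.

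- **Outcomes.** Under Primary and secondary endpoints: "The surgical outcomes will include operative duration, intraoperative blood loss, intraoperative blood transfusions, stone distribution and SO function". They are secondary: "The secondary outcomes will be the surgical, perioperative and long-term follow-up outcomes". No start or stop point is given for duration, blood loss or transfusion.
- **Time of allocation.** Under Randomization and blinding: "The envelopes will be opened after common bile duct exploration". The same section restricts assignment to eligible patients: "Patients meeting the eligibility criteria will be randomly assigned (1:1) to the T-tube drainage arm or Roux-en-Y HJ arm".
- **Surgery that eligibility requires.** The Inclusion criteria ask for "foci removal, stone extraction without residue and stricture correction" during the operation. Trial interventions adds: "All patients with SOL underwent common bile duct exploration and complete stone extraction".
- **What differs by arm.** Only the drainage step is described separately: T-tube placement with duct suture in Group A, the Roux-en-Y reconstruction in Group B.
- **Why the shared part varies.** Some patients have a liver resection and some do not. Standardization of perioperative care begins its list of reasons thus: "Indications for liver lobe resection will include a liver segment or lobe filled with stones that were inaccessible by other approaches for treatment".
- **Analysis.** Under Statistical analysis, continuous outcomes go to Student's t "test and the non-parametric Mann-Whitney" U test, and categorical outcomes to Fisher's exact test. A logistic model is named only for biliary complications. No covariate is named for the surgical outcomes.

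**The concern.** Whatever happens before the envelope is opened cannot depend on the arm. If duration and blood loss run from incision to closure, each patient's value is the sum of a part that the drainage method can influence and a part that it cannot. The second part may be large and variable, because it includes exploration, clearance and, on the apparent order of steps, any resection.

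An unadjusted two-group test puts all of that variation into the standard error. If the two drainage procedures differ only modestly in time or blood loss, a non-significant result could then be read as equal surgical demands. The abstract gives evaluation of safety and perioperative outcomes as part of the trial's goal, so such a reading would be reported.

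The values needed to remove this variation exist only at one moment in theatre. A later analysis plan can specify adjustment, but it cannot recover blood loss at envelope opening if nobody wrote it down.

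**Working it through.** The plan gives no SD, expected difference or power for these outcomes, so there is no figure of its own to reproduce.

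**Inputs**
- From the article: 105 per group and 80% power (Number of patients needed); significance at P < 0.05 (Statistical analysis), taken as two-sided.
- Assumed: SD after the envelope 30 min; SD before it 60 min, range 30 to 90; the two parts independent.

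**Formulas**
- Whole-operation SD = √(SD_pre² + SD_post²). Central case: √(60² + 30²) = 67.1 min.
- SE of the arm difference = SD × √(2/105). Central case: 9.26 min. Post-envelope part alone: 30 × √(2/105) = 4.14 min.
- Detectable difference = (1.96 + 0.84) × SE = 2.80 × SE.
- Power for a true difference Δ = Φ(Δ/SE − 1.96).

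| SD before envelope (min) | SD compared | SE | Detectable difference | Power, Δ = 15 | Δ = 30 | Δ = 45 |
|---|---|---|---|---|---|---|
| excluded (post-envelope only) | 30 | 4.14 | 11.6 | 95% | >99.9% | >99.9% |
| 30 | 42.4 | 5.86 | 16.4 | 73% | 99.9% | >99.9% |
| 60 | 67.1 | 9.26 | 25.9 | 37% | 90% | 99.8% |
| 90 | 94.9 | 13.1 | 36.7 | 21% | 63% | 93% |

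**Bias.** In 20,000 simulated trials with a true difference of 45 min and SDs of 60 before and 30 after, the mean estimate was 45.0 min for both the whole operation and the post-envelope part. The standard errors were 9.3 and 4.1 min. Pre-allocation surgery changes the precision and not the expected difference.

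**Adjustment.** Total = pre + post. Under independence, regressing the total on arm and the pre-envelope value leaves a residual SD of 30 min. The adjusted comparison of totals then has a detectable difference of about 12 min, without changing the outcome.

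**Transfusion yes/no.** Let a share q in each arm be transfused before allocation, and let p_A and p_B be the risks of a later transfusion among the rest. The whole-operation risks are q + (1 − q)p_A and q + (1 − q)p_B, so the risk difference is (1 − q)(p_B − p_A). It shrinks by the factor 1 − q, which is a dilution and not only a loss of precision. A Mann-Whitney comparison of skewed blood loss is diluted on the rank scale in a similar way.

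**The case against.** The strongest reply is that the article never says the outcomes cover the whole operation. It leaves the window open, and a full protocol or CRF, which the article says is available on request, may settle it. That stands. The point therefore rests on the natural reading of the terms, and nothing in the text is contradicted.

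The size of the problem is also uncertain. Every SD is assumed, and Group B involves duct transection and two anastomoses against one short step in Group A, so the true difference may be large. At the central SDs, power is 90% for 30 min and 99.8% for 45 min. This stands too, and it limits the point to modest differences or a large pre-envelope SD.

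The order of steps is partly inferred. The envelope is placed only after exploration, and no sentence puts hepatectomy before it. Nor is the post-envelope segment a clean measure for transfusion, since blood given later may replace blood lost earlier. Both are reasons to keep the totals and adjust them, not to replace them. Whole-operation totals are valid outcomes, since the patient undergoes the whole operation.

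Two stronger readings are tempting, and the documents support neither.
- A reader might infer that the pre-allocation surgery hides the real difference between procedures. It does not bias the means, and no SD in the article shows that a real difference would be missed.
- A reader might infer that a chance imbalance in resections would pass as a treatment effect. The t test's standard error already includes that variation, so such false positives stay at the nominal 5%. The article also specifies hierarchical block randomisation without giving the strata, so balancing on resection cannot be ruled out.

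**Conclusion.** The point holds as one of precision on secondary outcomes. Read naturally, the plan compares whole-operation duration, blood loss and transfusion without adjustment, although part of each, possibly a large part, arises before allocation. The comparison of means remains valid.

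Under the assumed SDs, the detectable difference in time is about 26 min (16 to 37), against about 12 min once the pre-envelope part is removed. The loss is material for a difference of half a post-envelope SD (15 min), where power falls from 95% to 73%, 37% or 21% as the pre-envelope SD rises from 30 to 60 to 90 min. It is small for differences of 45 min or more. The same reasoning applies to blood loss, but the documents offer no basis for a figure. Only a yes/no transfusion outcome and rank-based comparisons are diluted as such.

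The result rests on the whole-operation reading, on clearance and foci removal preceding the envelope, and on independence of the two parts. The primary endpoint and the sample size are not touched.

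**What to change.** 1. State the measurement window for operative duration, blood loss and transfusion.
2. Record three values when the envelope is opened: clock time, cumulative blood loss and units transfused so far.
3. Keep the whole-operation totals as secondary outcomes, but compare them adjusted for the corresponding pre-envelope value, on a suitable scale if blood loss is skewed.
4. Report the segment from envelope opening to closure as a supporting analysis, with transfusion after allocation shown separately.
5. For patients already operated on (enrolment began on 1 February 2020), take the time of envelope opening from the anaesthetic record where possible. Otherwise adjust for liver resection (yes/no), but only where it was done before allocation; a resection after allocation is not a baseline variable.

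The cost is three extra CRF entries per operation, and blood-loss readings in theatre will be approximate. Adjustment on an imprecise reading recovers less than the full gain, but does not bias the arm comparison as long as the reading is taken before the allocation is known. No outcome is dropped and patient care does not change.
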